#### Randomization

In this study, dynamic allocation is used in order to ensure an even allocation of factors that may influence the evaluation of the efficacy of anti-hypertensive medications. Dynamic allocation will be performed at the registration/allocation center at the start of therapy, with respect to age, gender, and presence or absence of type II diabetes. The allocation table and the most recent breakdown of allocated subjects in each group will be used for dynamic allocation at the registration/allocation center. However, this allocation table and the information regarding the number of allocated subjects in each group will not be disclosed to the study representative, principal investigator, or investigator until the completion of the study.

The SAS dynamic allocation system will be used for subject registration and allocation. In this system, web-based e-mails and the SAS server owned by the National Cerebral and Cardiovascular Center are used to automatically register and allocate subjects on a 24-h basis without any human operators.

The principal investigator or investigator will obtain consent for participation in the study from the subjects who they consider will have no problems in participation. After confirming that a subject meets all the eligibility criteria, the principal investigator or investigator will enter the necessary items in the portable document format (PDF) version of the registration form and send it to the SAS dynamic allocation system by e-mail for registration. The SAS dynamic allocation system will check the received registration form to see whether or not the eligibility criteria are met and whether or not the subject is already registered. If there are no problems, the system will allocate the subject using the randomized minimization method based on allocation adjustment factors. The results of the allocation will be automatically sent to the e-mail address used to send the registration form. The principal investigator or investigator will start the treatment based on the notification and record it on the Case Report Form (CRF) for each subject.

#### Allocation factors

Dynamic allocation is performed with respect to the following factors:Age at the time of consent: younger than 65 years/65 years or olderGender: male/femaleConcomitant type II diabetes: present/absentPlaque to myocardium ratio (PMR): below 1.35/1.35 or higher in non-contrast T1-weighted CMR images of the main lesion (a cut-off point of PMR that separates high risk from intermediate risk) [24, 26]

#### Blinding

All imaging and laboratory data will be analyzed by an independent attending physician and a radiologist at the National Cerebral and Cardiovascular Center (Japan), including CMR and CTA measurements. These evaluators will be blinded to patient treatment status.

#### Data quality control and management

The principal investigator or investigator must complete CRFs for each subject who provides written informed consent. The study representative or a person designated by the study representative will authorize access to the electronic CRF system for the principal investigator or investigator. CRFs will be prepared in Japanese. Data will be directly entered into the electronic CRF system during CRF preparation. The principal investigator or investigator will confirm that CRFs are accurately and completely prepared and register the data in the electronic CRF system and other systems. The principal investigator will take full responsibility for the accuracy and reliability of all the data entered in the CRFs.

The completed CRFs are the property of the director of the study center. The principal investigator and other investigators must not disclose the information contained in the CRFs to third parties except for regulatory agencies without written approval from the director of the study center. Only investigators can access data.

#### Statistical methods

All the analysis will be made on an intent-to-treat (ITT) basis. The 2 g/day and the 4 g/day EPA/DHA groups will be compared against the no-treatment group for all primary analysis. For the primary outcome, treatment effects between the groups and their 95% confidence intervals are calculated from analysis of covariance (ANCOVA) models with adjustment for baseline values of the outcome measure. To confirm the conclusion from ITT-based analysis, the same analysis is repeated on a per-protocol set (PPS), where criteria for determining the PPS assignment would be established and confirmed by the Steering Committee. For secondary and other outcomes, we will use the chi-squared test for binary outcomes, and a *t* test for continuous outcomes. For subgroup analyses, we will use regression methods with appropriate interaction terms (respective subgroup × treatment group). Multivariable analyses will be based on logistic regression for binary outcomes and linear regression for continuous outcomes. We will examine the residual to assess model assumptions and goodness-of-fit.

All *p* values will be reported to four decimal places with *p* values less than 0.001 reported as *p* < 0.001. Up-to-date versions of SAS (SAS Institute, Cary, NC, USA) will be used to conduct analyses. For all tests, we will use two-sided *p* values with an alpha ≤ 0.05 level of significance

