### Study design

This is a single-center, triple-arm, parallel-group, randomized controlled, open-label, superiority trial examining the effect of 12 months of EPA/DHA therapy on coronary HIPs in patients with CAD between May 2014 and April 2018. Eligible subjects are randomly assigned to the 2 g/day EPA/DHA group, the 4 g/day EPA/DHA group, or the no-treatment group (allocation rate 1:1:1). The randomization stratified on following variables (age, gender, presence or absence of type 2 diabetes mellitus, and PMR of the primary coronary lesion measured with non-contrast T1WI) (Fig. 1).

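### The primary ANCOVA leaves out age group, sex and type 2 diabetes, on which patients are minimised; if these predict PMR change, its standard errors are somewhat too large

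*Protocol article*

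**What the plan says.** The Randomization section of the protocol article states that "the system will allocate the subject using the randomized minimization method based on allocation adjustment factors". The Allocation factors section opens "Dynamic allocation is performed with respect to the following factors" and lists four: age at consent (under 65, or 65 and over), gender, concomitant type II diabetes, and PMR, split "below 1.35/1.35 or higher in non-contrast T1-weighted CMR images of the main lesion". Study design names the same four: "age, gender, presence or absence of type 2 diabetes mellitus, and PMR of the primary coronary lesion measured with non-contrast T1WI". The first paragraph of Randomization names only three, saying that allocation is done "with respect to age, gender, and presence or absence of type II diabetes". It gives the purpose as "to ensure an even allocation of factors that may influence the evaluation of the efficacy", there tied to anti-hypertensive drugs, which this trial does not test.

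For the primary outcome, Statistical methods specifies analysis of covariance ("ANCOVA) models with adjustment for baseline values of the outcome measure"). No other covariate is named. The later sentence on multivariable regression in that section is tied neither to the primary outcome nor to the allocation factors.

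**The concern.** Minimisation forces the arms to be alike on the chosen factors. If such a factor predicts the outcome, balancing it removes part of the chance variation between arms. A model that omits the factor does not register this: the factor's contribution stays in the residual variance, and the standard error is computed as if the factor had been left to chance. The reported precision is then worse than the precision achieved.

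What is at stake is efficiency and the accuracy of the confidence intervals. The protocol itself treats these factors as possibly influential on the efficacy evaluation, which is its reason for balancing them. The three-factor list in Randomization adds a smaller question: the factor missing from it is the baseline of the primary endpoint.

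**Working it through.** **The plan's own figure.** Inputs from Sample size: difference 0.15, SD 0.2, one-sided 1.25% per comparison, 46 per group. The standard error of a two-arm difference is 0.2 × √(2/46) = 0.0417. Exact noncentral-t power is 0.897 at 45 per group and 0.904 at 46, so 46 is the smallest size reaching 90%. The sample size reproduces and is unaffected by this point.

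**Size of the effect.** Let R² be the share of the variance in PMR change, after baseline PMR, that age group, sex and diabetes explain. The protocol gives no value, so a range is assumed. With the factors balanced, the standard error without them divided by that with them is 1/√(1 − R²):

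- R² = 0: 1.00
- R² = 0.05: 1/√0.95 = 1.03
- R² = 0.10: 1/√0.90 = 1.05
- R² = 0.20: 1/√0.80 = 1.12

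**Simulation at the 5% level.** This used 138 patients in three arms, minimisation on all four factors with probability 0.8 for the best arm, no treatment effect, 2,000 trials with both comparisons counted, and a nominal two-sided 5% level. Further assumptions, none from the protocol: 60% aged 65 or over, 20% in the smaller sex group, 35% diabetic, a skewed baseline PMR starting at 1.0, and the three factors contributing equally.

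| R² | Baseline-only: true SD of estimate | Baseline-only: mean model SE | Baseline-only: type I error | Factors added: mean model SE | Factors added: type I error |
|---|---|---|---|---|---|
| 0 | 0.0416 | 0.0417 | 4.8% | 0.0417 | 5.0% |
| 0.05 | 0.0407 | 0.0417 | 4.3% | 0.0407 | 5.0% |
| 0.10 | 0.0397 | 0.0417 | 4.1% | 0.0396 | 5.0% |
| 0.20 | 0.0377 | 0.0418 | 3.0% | 0.0373 | 5.0% |

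The planned model's SE stays near 0.0417 while the true spread of its estimate shrinks. At R² = 0.10 it overstates the spread by 0.0417/0.0397 = 1.05, and at 0.20 by 0.0418/0.0377 = 1.11. With the factors added, SE and type I error are right.

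**Power.** A separate simulation (4,000 trials, 46 per arm on average, two-sided 2.5%, which matches one-sided 1.25%) gave:

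| R² | Baseline-only | Factors added | Difference |
|---|---|---|---|
| 0.05 | 91.6% | 92.7% | 1.1 points |
| 0.10 | 92.5% | 93.9% | 1.4 points |
| 0.20 | 93.5% | 96.2% | 2.7 points |

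Its type I errors are weaker evidence. Even the model with the factors came out at 2.0% against a nominal 2.5%, about two Monte Carlo standard errors low (√(0.025 × 0.975/4000) = 0.25 points). The type I argument therefore rests on the table at the 5% level.

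**Cost.** The planned model has four parameters (intercept, two treatment terms, baseline PMR), leaving 138 − 4 = 134 residual degrees of freedom. Three more terms leave 131.

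**The factor lists.** Study design and Allocation factors agree on four factors, and the latter gives cut-points. Only the sentence in Randomization has three. If PMR were in fact left out, the SD of the between-arm difference in the share at 1.35 or above would be √(2 × 0.4 × 0.6/50) = 0.098, or about 10 percentage points, assuming 40% of patients fall in that stratum.

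**The case against.** The strongest reply is that the effect is conditional and its size unknown. It needs age, sex and diabetes to predict PMR change beyond baseline PMR, and the protocol says only that the factors may be influential. At R² of 0.05 to 0.10 the SE is 3% to 5% too large, and the error is in the safe direction. The allocation factor closest to the outcome, baseline PMR, is already in the model. All of this stands, and it limits the point to one of modest efficiency.

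It can also be said that an article condenses its analysis plan. That carries less weight here, because the article states the adjustment set, and a plan that added the factors would depart from it.

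A reader might infer three stronger things that the document does not support:

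- **That the trial loses its power.** Baseline-only power stays above the 90% target throughout the range examined and rises with R². What is forgone is a further 1 to 3 points.
- **That baseline PMR might not be balanced at all.** Even without PMR in the scheme, randomisation balances it in expectation, and the ANCOVA adjusts for chance imbalance.
- **That the allocation system must be misprogrammed because the lists differ.** Randomization does not call its three factors exhaustive and later refers to allocation adjustment factors in general. The section that follows lists all four. It is an incomplete sentence, not evidence of a programming error.

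**Conclusion.** The point holds as a conditional matter of precision. Three of the four minimisation factors are missing from the stated primary model. If they are prognostic after baseline PMR, the model-based SE is too large by about 3%, 5% or 12% relative to the model that includes them, at assumed R² of 0.05, 0.10 and 0.20. The intervals are then wider than they need be and the test runs below its nominal level. If they are not prognostic, nothing is lost. The treatment estimate is unbiased either way and false positives are not inflated.

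The direction follows from the design. The size rests on the assumed R² and, for the simulated figures, on the assumed prevalences and minimisation probability. The change is worth making because it costs almost nothing, not because the planned analysis is invalid. The incomplete factor list in Randomization is a minor correction.

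**What to change.** Before the data are analysed, specify the primary model as change in PMR on treatment (three levels), continuous baseline PMR, age group (under 65, or 65 and over), sex and type 2 diabetes. Use the same model for the per-protocol repeat. This takes one line of wording and three degrees of freedom out of 134.

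In Randomization, add PMR to the factor list so that it agrees with Study design and Allocation factors, and remove the reference to anti-hypertensive drugs. Confirm once that the allocation system uses the four factors and cut-points in Allocation factors. This takes one corrected paragraph and one check.

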### Study procedures

Eligible patients are randomly assigned to the 2 g/day EPA/DHA group, the 4 g/day EPA/DHA group, or the no-treatment group. Prospective, serial, non-contrast T1WI and CTA examinations are performed at baseline and after 12 months of EPA/DHA treatment (Fig. 2).

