#### Other variables

Change and percentage change in triglycerides, total cholesterol, LDL-cholesterol, high-density lipoprotein (HDL)-cholesterol, non-HDL-cholesterol, very-low-density lipoprotein (VLDL)-cholesterol, remnant-like lipoprotein cholesterol, lipoprotein lipase (LPL) activity, and high-sensitivity C-reactive protein from baseline to study completion or discontinuationChange and percentage change in small, dense LDL and mean LDL particle diameter from baseline to study completion or discontinuation (LDL diameter is measured using Lipoprint^TM^ system (Quantimetrix))Change and percentage change in EPA, DHA, arachidonic acid (AA), EPA/AA ratio, and LC n-3 PUFA (percentage of EPA [C20:5ω3] and DHA [C22:6ω3] by weight in all fatty acids out of all lipids) from baseline to study completion or discontinuationChange and percentage change in leptin and adiponectin from baseline to study completion or discontinuation

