#### Sample size

Based on the result from our previous study, a clinically meaningful change from baseline in PMR was assumed to be − 0.15 in both the 2 g/day and the 4 g/day LC n-3 PUFA groups, and no change in the no-treatment group, with a common standard deviation of 0.2 among the groups. The sample size per group of 46 archives 90% power to detect the assumed difference in changes, using a two-group, one-sided *t* test of 1.25% significance level, where the overall significance level of the one-sided test for the two comparisons (i.e., the 2 g/day group versus the no-treatment group, and the 4 g/day LC n-3 PUFA group versus the no-treatment group) was 2.5% and the Bonferroni adjustment was applied to control the Type I error rate. Allowing for adjustment of withdrawals, missing data or loss to follow-up, 50 subjects per group will be recruited into the trial.

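### Continuous secondary and other outcomes are tested without their measured baseline, while the primary outcome is baseline-adjusted: valid, but less precise than the data allow

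*Protocol article*

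**What the plan says.** The Statistical methods section of the protocol article sets two standards for continuous outcomes.

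- **Primary outcome** (change in PMR of the primary lesion): treatment effects come from "analysis of covariance (ANCOVA) models with adjustment for baseline values of the outcome measure".
- **All others:** the secondary and other outcomes get "a *t* test for continuous outcomes". No covariate, transformation or rank-based alternative is named.

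The outcomes under the second rule are listed in Table 1 and in the Secondary endpoint and Other variables sections. They are PMR in all lesions, percentage change in PMR, the CTA measures, and a laboratory panel that begins "Change and percentage change in triglycerides, total cholesterol, LDL-cholesterol" and goes on to remnant cholesterol, hs-CRP, leptin and adiponectin. All are changes or percentage changes from baseline. For the imaging outcomes, Study procedures confirms that the "examinations are performed at baseline and after 12 months of EPA/DHA treatment".

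Two further sentences in Statistical methods bear on the point: "Multivariable analyses will be based on logistic regression for binary outcomes and linear regression for continuous outcomes", and "We will examine the residual to assess model assumptions and goodness-of-fit".

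**The concern.** A t test on change subtracts the whole baseline value, as if follow-up moved one for one with it. When the true slope is below one, the subtraction overcorrects, and the leftover dependence on baseline stays in the residual as noise. Any chance difference between arms at baseline also carries into the estimate in a given trial. ANCOVA estimates the slope and removes both.

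The plan already uses ANCOVA for one outcome, so the contrast is within a single section. Change in primary-lesion PMR is baseline-adjusted, while percentage change in PMR of the same lesion, from the same two scans, is not. The two results could differ partly because the model changed.

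At stake are wider confidence intervals than necessary for the CTA, all-lesion PMR, lipid and inflammatory results, in a trial with 50 patients per group that describes itself as exploratory.

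**Working it through.** **1. The plan's own figure.** The Sample size section assumes a PMR difference of 0.15, an SD of 0.2, a one-sided 1.25% level and 90% power. The normal approximation gives n = 2 × (2.241 + 1.282)² × (0.2/0.15)² = 44.1, so 45 per group. The exact t-test power is 89.7% at 45 and 90.4% at 46. The stated 46 is reproduced, and 46/(1 − 0.08) = 50. Nothing below disputes this; 46 per group is used only as the evaluable number.

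**2. Variance of the two estimators.** Assume one value per patient, the same SD s at baseline and follow-up, and within-arm correlation r.

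- Change score, per-patient variance: 2(1 − r)s²
- ANCOVA, residual variance: (1 − r²)s²
- Ratio: (1 − r²) / [2(1 − r)] = (1 + r)/2

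The protocol gives no r. Over an assumed range:

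| r | Variance ratio | CI width ratio | ANCOVA n per group matching 46 by t test | ANCOVA power where t test has 80% |
|---|---|---|---|---|
| 0.5 | 0.75 | 0.87 | 35 | 90% |
| 0.6 | 0.80 | 0.89 | 37 | 88% |
| 0.7 | 0.85 | 0.92 | 40 | 86% |
| 0.8 | 0.90 | 0.95 | 42 | 84% |

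The fourth column is 46 × ratio, rounded up (46 × 0.75 = 34.5, so 35).

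**3. Does the direction depend on equal variances?** With SDs s₀ at baseline and s₁ at follow-up, the change-score variance minus the ANCOVA variance is (s₀² + s₁² − 2r s₀s₁) − s₁²(1 − r²) = (s₀ − r s₁)². This is never negative. Apart from one degree of freedom, ANCOVA is therefore never less precise. The gain vanishes only when the slope r s₁/s₀ equals one, which under equal variances means r = 1.

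These formulas are for absolute change. They do not give the gain for percentage change.

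**4. Skewed laboratory markers.** The protocol gives no laboratory distributions, so this step is illustrative. A log-normal marker was simulated with 46 per arm, two-sided 0.05 and 3,000 runs per scenario. Power was:

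| Log SD | r (log scale) | Reduction | t, change | t, % change | t, log change | ANCOVA, log |
|---|---|---|---|---|---|---|
| 0.5 | 0.5 | 20% | 0.45 | 0.52 | 0.56 | 0.68 |
| 0.5 | 0.7 | 20% | 0.63 | 0.75 | 0.77 | 0.84 |
| 1.0 | 0.5 | 35% | 0.27 | 0.38 | 0.53 | 0.66 |
| 1.0 | 0.7 | 35% | 0.39 | 0.65 | 0.76 | 0.83 |

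The step from raw change to log change is the effect of scale; the step from log change to log ANCOVA is the effect of baseline adjustment. In the third row these are 0.53 − 0.27 = 0.26 and 0.66 − 0.53 = 0.13. Scale is the larger part in three rows, and the two are about equal in the first. With no treatment effect, rejection rates were 0.036 to 0.049 for the t tests on change and percentage change.

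**The case against.** **The t test is not wrong.** Under randomisation it is unbiased, and the simulated type I error was not inflated. This stands. A reader might infer that the secondary results would be invalid or prone to false positives; neither the protocol nor the calculations support that.

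**Adjusted models and residual checks are already planned.** This is only partial mitigation. The regression sentence is not tied to the secondary outcomes and does not name baseline as a covariate, and no consequence of a poor residual check is stated. The t test remains the stated analysis. The point therefore concerns a choice the article makes, not detail left to an unseen SAP.

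**Skewness is a different matter.** How to transform laboratory markers is commonly left to the SAP, and the article does not rule out a log scale. This stands. A reader might also take a contrast such as 24% power (t test on raw change) against 56% (log ANCOVA), obtained at an assumed log SD of 1.0, r = 0.6 and a 30% reduction, as the cost of omitting baseline. It is not: a plain t test on log change already reaches 47% there, so about 23 of the 32 points come from the scale and about 9 from baseline. With mild skew (log SD 0.2, r = 0.8, 10% reduction), the t tests on change and percentage change reach 96% and 98%, against 98% for log ANCOVA.

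**Allocation limits imbalance.** The Allocation factors section includes main-lesion PMR at a cut-off of 1.35, which restrains baseline differences in that measure. It does little for the CTA and laboratory variables, and it does not remove the variance in step 2.

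**Conclusion.** The point holds as one of efficiency and consistency. The plan fixes an unadjusted test for every continuous secondary and other outcome, although each baseline is measured and the same section adjusts the primary outcome.

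For absolute changes, ANCOVA variance would be 0.75 to 0.90 of the t-test variance for an assumed r of 0.5 to 0.8 with equal variances, or confidence intervals about 5% to 13% narrower. Confidence is high in the direction, which is algebraic, and limited in the size, because no r is given. The loss on skewed markers rests on assumed distributions and belongs mainly to the choice of scale.

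It would go too far to say that the trial's conclusion or its sample size is at risk: the primary outcome already has baseline-adjusted ANCOVA, and the 46 per group reproduces.

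**What to change.** Replace the t-test rule for continuous outcomes: analyse each secondary and other continuous outcome by ANCOVA with its own baseline value as covariate, in the same form as the primary analysis. Baseline alone is enough for consistency, since the primary model names no other covariate.

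Optionally, for laboratory markers expected to be right-skewed, such as triglycerides, remnant cholesterol and hs-CRP, prespecify ANCOVA of log follow-up on log baseline. Report the back-transformed ratio alongside the listed percentage change, not in its place. A ratio of geometric means and a mean percentage change are different summaries, and substituting one for the other would alter a listed outcome.

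The main change costs one sentence, needs no new data and uses one degree of freedom per model. The optional part adds a short list of markers and one more reported summary for each. Both should be settled before outcome data by group are seen, so that the choice of model cannot appear data-driven.

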We have reported that coronary high-intensity plaques (HIPs) detected with non-contrast T1-weighted imaging (T1WI) on cardiac magnetic resonance (CMR) are associated with computed tomography angiography (CTA) – and intravascular ultrasound-derived – features of high-risk plaques [22, 23]. HIPs, which can be uniquely assessed using the plaque-to-myocardium signal intensity ratio (PMR), [22] are significantly associated with future coronary events [24]. More recently, in the AQUAMARINE (Attempts at Plaque Vulnerability Quantification with Magnetic Resonance Imaging Using Non-contrast T1-weighted Technic) study, we have demonstrated that intensive lipid-lowering therapy with pitavastatin reduces the PMR of coronary HIPs by approximately 25% [25]. Thus, non-contrast T1WI is now being established as a less-invasive technique for evaluating high-risk coronary plaques, and as such, might be a promising predictive factor in patients at high risk.

The present AQUAMARINE-EPA/DHA study is designed to assess the anti-atherogenic effect of EPA/DHA in an exploratory manner. We will study the change in PMR of coronary HIPs detected using CMR after 12 months of EPA/DHA therapy.

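### The two-sided 0.05 rule covers every secondary, other and subgroup test with no link to the primary result; it should be limited to the two primary dose comparisons

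*Protocol article*

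**What the plan says.** All references are to the protocol article.

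- **Criterion.** Statistical methods closes with: "For all tests, we will use two-sided *p* values with an alpha ≤ 0.05 level of significance".
- **Tests under that criterion.** The same section says "For secondary and other outcomes, we will use the chi-squared test for binary outcomes, and a *t* test for continuous outcomes". On subgroups it says "For subgroup analyses, we will use regression methods with appropriate interaction terms (respective subgroup × treatment group"; the subgroups are not listed.
- **Pairs compared.** "The 2 g/day and the 4 g/day EPA/DHA groups will be compared against the no-treatment group for all primary analysis". The pairs are not restated for secondary or other outcomes.
- **Outcomes.** The article names one primary endpoint. It then lists secondary endpoints (PMR and CTA measures) and other variables, for example "Change and percentage change in triglycerides, total cholesterol, LDL-cholesterol" and "Change and percentage change in EPA, DHA, arachidonic acid (AA), EPA/AA ratio, and LC n-3 PUFA". This ranks the outcomes but gives no testing order.
- **Error control.** Sample size applies Bonferroni to the two dose comparisons on the primary endpoint: 2.5% one-sided overall, 1.25% each.
- **Status of the study.** The Background says it is "designed to assess the anti-atherogenic effect of EPA/DHA in an exploratory manner". Study design calls it a superiority trial.

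**The concern.** The sponsor recognised a multiplicity problem with two primary tests and split alpha for it. The same article then puts dozens of further tests at the full two-sided 0.05, with nothing tying them to the primary result. A CTA or laboratory measure could be called significant at one dose although the PMR comparison for that dose failed, and could then be offered as evidence of an anti-atherosclerotic effect.

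The secondary list adds to the risk because much of it is the same information twice: change and percentage change, primary lesion and all lesions. A chance result on one version tends to carry over to its near-copies, and several agreeing p values can look like corroboration.

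The primary conclusion, the sample size and the data are not at stake here. What is at stake is which other results may be called significant.

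**Working it through.** **1. The plan's own figure.** Inputs from Sample size: difference 0.15, SD 0.2, one-sided 1.25%, power 90%.

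- Normal approximation: n = 2 × (2.2414 + 1.2816)² × (0.2/0.15)² = 2 × 12.41 × 1.778 = 44.1, so 45 per group.
- Exact t test: power is 89.7% at 45 and 90.4% at 46, so 46 is reproduced.
- 46/(1 − 0.08) = 50, the number recruited per group.

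The 1.25% level is therefore the level the primary comparisons were sized for. The article gives no error rate for the remaining outcomes.

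**2. Counting the measures.**

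- Secondary endpoint: 3 PMR measures + 4 CTA measures × 2 scales × 2 lesion sets = 3 + 16 = 19.
- Other variables: 9 (lipids, LPL activity, C-reactive protein) + 2 (LDL size) + 5 (fatty acids) + 2 (adipokines) = 18, on 2 scales = 36.
- If both doses are compared with no treatment: 19 × 2 = 38 secondary tests and 36 × 2 = 72 other tests.

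**3. Secondary tests, independence as the upper reference.** Chance of at least one false positive = 1 − 0.95^m.

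- One dose, m = 19: 62.3%.
- Both doses, m = 38: 85.8%.
- Expected number at both doses: 38 × 0.05 = 1.9, whatever the correlation.

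**4. Secondary tests with the near-duplicates modelled.** The article gives no correlations, so these are assumed. There are five measures (PMR, Hounsfield units, plaque volume, vessel area, plaque area), two lesion sets and two scales, less the primary endpoint itself, which leaves 19. The correlation between two outcomes is the product of the factors on which they differ. Three equal arms share one control, z tests are two-sided at 0.05, and there are 100,000 simulated trials with no true effect.

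| Between measures | Primary vs all lesions | Change vs % change | Both doses (38 tests) | One dose (19 tests) |
|---|---|---|---|---|
| 0 | 0.5 | 0.9 | 70.1% | 48.0% |
| 0.3 | 0.7 | 0.95 | 60.2% | 39.4% |
| 0.5 | 0.8 | 0.95 | 52.0% | 32.8% |
| 0.7 | 0.9 | 0.98 | 38.0% | 23.1% |
| 0.8 | 0.95 | 0.99 | 29.9% | 17.5% |

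**5. Clustering.** The mean stays at 1.9, so the average number of false positives, given at least one, is 1.9 divided by the chance of any. That is 1.9/0.701 = 2.7 in the first row and 1.9/0.299 = 6.4 in the last. Higher correlation makes a false positive rarer, but more of them then appear together.

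**6. Not computed.** No rate is given for the 72 other tests. The Background and Discussion expect triglycerides and remnant lipoproteins to fall, and blood fatty acids follow intake, so a null for all of them is not credible. Subgroup tests cannot be counted because no subgroups are named.

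**The case against.** The strongest reply is that multiplicity for secondary outcomes is usually left to the analysis plan, which is not at hand, and that a journal article condenses. On that view, the lack of a hierarchy alone would be no finding. But the article is not silent: it names the tests and fixes their significance level. A later plan that barred significance claims on these outcomes would have to override that sentence.

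The second reply is that the Background already calls the study exploratory. A reader might infer that the outcomes carry no exploratory label at all; that would be wrong. The label is on the whole study, primary endpoint included, and it sits beside a superiority design with a Bonferroni-controlled primary. It does not separate the secondary outcomes from the primary or limit what may be called significant.

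Three further limits stand:

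- **Both doses.** This is inferred for secondary outcomes. It is the natural reading of a two-group t test in three arms, but only the primary analysis states it. The one-dose figures are given for that reason.
- **More likely than not.** A reader might infer that a false secondary finding is probable. For the secondary set the chance is above one half in three of the five settings at both doses, and in none at one dose.
- **A breached 5%.** A reader might set these rates against the stated 0.05. They are familywise rates, 0.05 is a per-test level, and the article states no familywise level for secondary outcomes.

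It is also true that the harm lies in later reporting, and that nominal testing of secondary outcomes is common in a single-center imaging trial. That limits the weight of the point but does not remove it.

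**Conclusion.** The point holds in a limited form. The stated rule allows each of the 19 secondary and 36 other measures, and any subgroup interaction, to be called significant at two-sided 0.05 with no reference to the primary result. The only Type I error control covers the two primary dose comparisons.

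For the secondary set at both doses, the chance of at least one false positive is about 30% to 70% when neither dose affects any of these measures, with 1.9 expected. At one dose it is 18% to 48%. The ranges rest on assumed correlations, and the higher one also on the inference that both doses are tested.

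The article does not support a claim that a false secondary result is certain or even probable, a figure for the laboratory or subgroup tests, or any effect on the validity of the primary test. The difference between two-sided 0.05 for all tests and the one-sided 1.25% used to size the primary is a separate matter in the same sentence. This is a correction that should be made, not one on which the trial depends.

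**What to change.** Rewrite the last sentence of Statistical methods so that:

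- the significance rule applies only to the two primary comparisons of each dose with no treatment, at the level set under Sample size;
- secondary, other and subgroup results are called exploratory and reported as estimates with nominal 95% confidence intervals;
- none of them can support an efficacy conclusion for a dose whose primary comparison fails.

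The cost is a few sentences in the protocol or analysis plan, with no added patients, data or procedures. The downside is that an isolated p value below 0.05 on these outcomes can no longer be presented as a significant finding.
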